#### Secondary Outcomes

Regarding the results of the secondary measures of the study, it is expected significant increasing scores in quality of life and posttraumatic growth and decreasing scores in anxiety and depression, fatigue and insomnia from T0 to T1 and these scores remain stable in the follow up assessment (T2 and T3) in the face to face ACT + app group. As with psychological flexibility, it is expected that the mean scores of the face-to-face ACT + app group achieve statistically significant higher values in quality of life and posttraumatic growth and significantly lower scores in anxiety, depression, fatigue and insomnia at T1, T2, and T3 when compared with the face-to-face ACT group and the waitlist group. Finally, it is expected that the mean scores of the face-to-face ACT group in quality of life and posttraumatic growth will be significantly higher, and the scores in anxiety, fatigue and insomnia will be significantly lower, when compared with the scores obtained by the waitlist group at the three assessment points.

#### Participant Timeline

Time schedule of recruitment, interventions, assessment, and follow-ups are available in the flow diagram (see Figure 2).

**FIGURE 2 F2:**
[figure not shown]
Schedule of enrollment, interventions, and assessments. *Recommended content can be displayed using various schematic formats. See SPIRIT 2013. Explanation and Elaboration for examples from protocols. **List specific timepoints in this row.

### Sample Size

To determine the optimal sample size, we considered the effect sizes in psychological flexibility obtained in previous works by other authors. A recent meta-analysis (Chunxiao et al., 2020) examined the effect of ACT (including face-to-face and internet-based modalities) on psychological flexibility compared with treatment as usual or waitlist in cancer patients. The results showed a moderate effect size (Hedges’ *g*) of 0.58 at post-treatment. Taking into account these results, a medium effect size of 0.5 (Cohen’s *d*) has been assumed to detect differences between the interventions and waitlist group. Since no software to determine sample size for linear mixed model analyses was available, we used the *f* index of G*Power. Therefore, an effect size of 0.25 (index f) is assumed, equivalent to Cohen’s *d* = 0.5. Thus, with a statistical power of 0.80, an alpha level of 0.05 and a correlation between repeated measures of 0.5, a total sample of 102 participants is required (34 subjects in each group). In order to control the lack of participants during the intervention and evaluation process, based on a previous study (Arch and Mitchell, 2016) we assume a dropout rate of 10%. Consequently, we require to include 112 participants in our study (38 participants per group).

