1.The combined intervention (face-to-face ACT + app) will be more effective in increasing psychological flexibility, quality of life and post-traumatic growth and reducing symptoms of anxiety, depression, fatigue and insomnia than the face-to-face ACT intervention at posttreatment and at the two follow-up periods (3 and 6 months).2.The face-to-face ACT + app group will achieve significant improvements in psychological flexibility, quality of life and post-traumatic growth and significant reductions in anxiety, depression, fatigue, and insomnia compared to the waitlist group after the intervention and at the two follow-up periods (3 and 6 months).3.The face-to-face ACT intervention group will significantly increase psychological flexibility, quality of life and post-traumatic growth, and reduce symptoms of anxiety, depression, fatigue, and insomnia compared to the waitlist group after the intervention and at the two follow-up periods (3 and 6 months).

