One of the strengths of this protocol is the inclusion of a significant number of participants, which results from the estimation of the adequate sample size to obtain significant results based on previous studies. Also, the inclusion of cancer patients with different diagnoses can help to broaden the knowledge about the efficacy of ACT in oncological settings, which may increase its applicability. Furthermore, the use of a randomized, controlled, two-follow-up design can help establish the long-term efficacy of the intervention.

Notwithstanding, it is necessary to mention some of the limitations that may appear when carrying out this study. First, the inclusion of patients with different diagnoses and treatments may influence the results obtained, since there may be different strategies and effects of the treatments that influence the results. Furthermore, to avoid loss of participants in the waitlist group, the intervention in this group will start immediately after completion in the two ACT groups and this circumstance may limit the information about the long-term effects of the intervention.

Despite these limitations, the results that are expected to be obtained after conducting this trial may be useful in helping patients during their treatment to reduce symptoms that appear frequently during the course of the disease and that can negatively affect their daily life.

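### The stated 80% power is not tied to the pairwise, visit-specific hypotheses: at d = 0.5 with 34 per arm these have about 0.53 to 0.65, and ACT + app versus ACT has no assumed effect

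*Protocol article*

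**What the plan says.** The Sample Size section starts from a meta-analytic Hedges' g of 0.58 at post-treatment, for ACT against usual care or waitlist in cancer patients. It rounds this down to d = 0.5, which "has been assumed to detect differences between the interventions and waitlist group". It explains the tool used: "Since no software to determine sample size for linear mixed model analyses was available", the f index of G*Power was taken instead. Then: "Therefore, an effect size of 0.25 (index f) is assumed, equivalent to" d = 0.5. The remaining inputs are "with a statistical power of 0.80, an alpha level of 0.05 and a correlation between repeated measures of 0.5", and the result is 102 in total, 34 per arm, raised to 38 per arm for 10% dropout. The G*Power procedure and the number of measurements entered are not given.

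The hypotheses at the end of the Introduction are pairwise and apply at post-treatment, 3 months and 6 months. The first reads "The combined intervention (face-to-face ACT + app) will be more effective in increasing psychological flexibility", with face-to-face ACT as the comparator; the other two set each ACT arm against waitlist. Primary Outcomes repeats these contrasts for the AAQ-II. Statistical Methods plans mixed linear models over all visits. Study Design and Settings places T0 before randomisation. The Discussion lists the sample as a strength, "which results from the estimation of the adequate sample size to obtain significant results based on previous studies".

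**The concern.** A power statement is useful only if it belongs to the comparison that will be interpreted. Here there are three mismatches.

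- The sample size appears to come from an omnibus test averaged over visits, while the hypotheses are pairwise and by visit.
- The effect size is converted with a formula for two groups in a three-arm trial.
- The assumed effect is justified for ACT against usual care or waitlist only, although the first hypothesis concerns what the app adds to ACT.

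What is at stake is how a non-significant result is read. If the trial is taken as adequately sized for every hypothesis, a null finding for the app would be read as evidence of no added benefit, and the protocol contains no calculation to support that reading.

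**Working it through.** **Inputs.** From Sample Size: f = 0.25, d = 0.5, alpha 0.05, power 0.80, correlation ρ = 0.5, N = 102 (34 per arm, 38 with dropout). From Study Design and Settings: k = 3 arms at 1:1:1, and m = 4 assessments. Two-sided tests are assumed for the pairwise contrasts, since sidedness is not stated. No multiplicity adjustment is applied.

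**1. Reproducing 102.** For the repeated-measures between-factors F test, λ = N·m·f² / (1 + (m − 1)ρ), with k − 1 and N − k degrees of freedom.
- N = 102: λ = 102 × 4 × 0.0625 / 2.5 = 10.2, df 2 and 99, power 0.811.
- N = 99: λ = 9.9, power 0.798.

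So 102 is the smallest total with equal arms that reaches 0.80. Other procedures with the same inputs give other totals:

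| Procedure | N |
|---|---|
| Between factors, 3 measurements | 108 |
| Between factors, 2 measurements | 120 |
| Within-between interaction, 4 measurements | 30 |
| One-way ANOVA at one visit | 159 |

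The interaction test in its SPSS-style form with three measurements also gives 102. It takes no correlation input, however, and the trial has four visits. The between-factors test is therefore the likely source, but this is an inference.

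**2. Converting d to f in three arms.** f = √[Σ(μᵢ − μ̄)² / k], in SD units. For means 0, 0.5, 0.5: μ̄ = 1/3, and f = √[(0.1111 + 0.0278 + 0.0278)/3] = 0.236. The relation f = d/2 = 0.25 holds for two equal groups. With f = 0.236 and N = 102, λ = 9.07 and power is 0.76.

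**3. Averaging over T0.** If the four measurements include T0, where randomised arms have no expected difference, the averaged difference is 0.5 × 3/4 = 0.375. Then f = 0.236 × 0.75 = 0.177, λ = 5.1 and power is 0.50.

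**4. Pairwise contrast at one visit, d = 0.5.** Noncentrality is d·√(n/2). Baseline adjustment at r = 0.5 multiplies the variance by 1 − 0.25 = 0.75, so d becomes 0.5/√0.75 = 0.577.

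| n per arm | Unadjusted | Baseline-adjusted |
|---|---|---|
| 34 | 0.53 (noncentrality 2.06) | 0.65 (2.38) |
| 38, no dropout | 0.58 | 0.70 |

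With 34 per arm, the d detectable at 80% power is about 0.69 unadjusted and 0.60 adjusted.

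**5. ACT + app against ACT.** The protocol gives no effect size. Assuming d = 0.2 to 0.3 for illustration, single-visit power with 34 per arm is 0.13 to 0.23 unadjusted and 0.16 to 0.29 adjusted.

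**6. The most favourable pairwise reading.** Take a baseline-adjusted contrast averaged over T1 to T3 with the same effect at each visit. The variance of the mean of three visits is (1 + 2 × 0.5)/3 = 2/3, and baseline adjustment removes 0.25, leaving 0.4167. Noncentrality is 0.5/√0.4167 × √17 = 3.19, and power is 0.88.

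**The case against.** The strongest defence is that the planned mixed model uses all visits, and that the averaged contrast in step 6 has power 0.88 at d = 0.5. On that reading the sample would suffice for ACT against waitlist. The arithmetic stands, but the reading does not fit the text. The hypotheses and Primary Outcomes name each visit, no averaged contrast is stated, and the cited g is a post-treatment effect. A constant effect against waitlist is also doubtful: under Waitlist Group these participants are offered ACT + app after the post-treatment assessment, and the Discussion says this starts immediately after the ACT groups finish.

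Two further points for the defence stand in part. The G*Power procedure is unnamed, so the omnibus attribution, and with it the 0.76 and 0.50, is inferred. And f = 0.25 is not impossible in three arms: means 0, 0.5 and 0.556 produce it. But that needs the app arm to exceed ACT by about 0.06 SD, which the section does not assume. With both arms at 0.5, the conversion alone moves power only from 0.81 to 0.76.

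A reader might go further and infer that 80% power applies to no hypothesis in the trial, or that the trial could hardly show an app effect. The documents do not support either. The first ignores the 0.88 under the averaged contrast; the second rests on an assumed d of 0.2 to 0.3 that is not in the protocol.

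**Conclusion.** The 80% figure is wrong as a statement about the hypotheses as written. For a pairwise difference at a single visit with 34 analysed per arm and d = 0.5, power is about 0.53 to 0.65, or 0.58 to 0.70 if all 38 per arm are analysed. This assumes two-sided alpha of 0.05, r = 0.5 and no multiplicity adjustment. It does not depend on which G*Power procedure was used.

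The equivalence of f = 0.25 and d = 0.5 is a two-group conversion and a smaller fault. The larger one is that ACT + app against ACT, the first hypothesis, has no assumed effect and so no stated power. The protocol gives no basis for reading a null result there as absence of benefit.

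**What to change.** Enrolment stays as planned.

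- Name the contrast that decides the primary outcome, and restate power for it. T1 is the natural visit: it precedes the offer of treatment to the waitlist arm and matches the cited post-treatment effect. If the contrast is the pairwise, baseline-adjusted AAQ-II difference at T1, state power of about 0.65 at d = 0.5 and a detectable d of about 0.60 at 80% power, with 34 per arm. If another contrast is chosen, compute power for that one.
- Name the procedure behind any retained G*Power figure, and delete the statement that f = 0.25 is equivalent to d = 0.5.
- State that no effect was assumed for ACT + app against ACT. Give power over a labelled range (about 0.13 to 0.29 at a single visit for d of 0.2 to 0.3), report the comparison as an estimate with a 95% confidence interval, and do not read a null result as no benefit.
- Remove the adequate-sample-size claim from the strengths in the Discussion.

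The cost is a rewritten sample-size paragraph and one Discussion sentence. The stated power becomes less favourable; no more patients are needed.

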## Methods and Analysis

### Study Design and Settings

This study is a three-arm randomized superiority clinical trial, with a pre-post-follow-up repeated measures intergroup design with a 1:1:1 allocation ratio. Participants will be randomly assigned to one of the following interventions: (1) face-to-face ACT + app, (2) face-to-face ACT and (3) Waitlist control group. For ethical reasons, the participants in the waitlist control condition will be offered the option to receive the treatment protocol. The evaluation will be carried out in four time points: initial evaluation before randomization (pre-treatment; T0), at the end of the intervention (post-treatment; T1), at 3 months after finishing the treatment (T2) and at 6 months after completing the intervention (T3) (see Figure 1).

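### The enrolment target gives two totals (112 overall, but 38 per group makes 114), and 112 less 10% dropout falls short of the 102 required

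*Protocol article*

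**What the plan says.** Study Design and Settings fixes the structure: "This study is a three-arm randomized superiority clinical trial", "with a 1:1:1 allocation ratio". Recruitment and Assignment to Interventions repeats the three conditions and the equal ratio.

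The Sample Size section then proceeds in three steps:

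- Required number: "a total sample of 102 participants is required (34 subjects in each group").
- Allowance for loss: "we assume a dropout rate of 10"%.
- Enrolment target: "Consequently, we require to include 112 participants in our study (38 participants per group").

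No other part of the article gives an enrolment total or explains the difference between the overall and per-group figures.

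**The concern.** There are two faults in the last step.

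First, the overall and per-group targets disagree. With three equal arms, the per-group number times three should be the total, and here it is not.

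Second, the total does not do what the section introduces it to do. The dropout allowance is meant to leave 102 participants after a 10% loss, and 112 leaves fewer.

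The enrolment target decides when recruitment stops and how long an allocation list is needed. It is also the natural yardstick for the yearly recruitment report described under Monitoring. A team that stops at 112 leaves at least one arm short of its stated 38, and a team that fills every arm to 38 overshoots the stated total. The Discussion names the sample size estimate as a strength of the protocol, so the figure should at least agree with itself.

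**Working it through.** **Inputs, all from the protocol article**

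| Input | Value | Section |
|---|---|---|
| Arms and allocation | 3, at 1:1:1 | Study Design and Settings |
| Measurements | 4 (T0 to T3) | Study Design and Settings |
| Effect size f | 0.25 | Sample Size |
| Power, alpha, correlation | 0.80, 0.05, 0.5 | Sample Size |
| Required number | 102 (34 per group) | Sample Size |
| Dropout | 10% | Sample Size |
| Enrolment target | 112 in total, 38 per group | Sample Size |

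**Step 1. Reproduce the 102.** The article names G*Power and the f index but not the test. A repeated-measures ANOVA, between-groups F test, has noncentrality λ = N·f²·m / (1 + (m − 1)ρ) with degrees of freedom (k − 1, N − k), where m is the number of measurements and k the number of groups.

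- At N = 102: λ = 102 × 0.0625 × 4 / (1 + 3 × 0.5) = 25.5 / 2.5 = 10.2, with 2 and 99 degrees of freedom. Power is 0.811.
- At N = 99, the next smaller multiple of three, power is 0.798.

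So 102 is the smallest total with equal groups that reaches 0.80, exactly as stated. The same test with three measurements gives 108, and the group-by-time interaction test with four gives 30, so the between-groups test with four measurements is the reading that fits. The 102 is a sound starting point for the dropout step.

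**Step 2. Inflate for dropout.** To keep n after losing a proportion d, enrol n/(1 − d).

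- Total: 102 / 0.90 = 113.3. Rounded up to a multiple of three, this is 114.
- Per group: 34 / 0.90 = 37.8. Rounded up, this is 38.
- Check: 3 × 38 = 114.

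The printed 38 agrees with the correct method.

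**Step 3. Where 112 probably comes from.** 102 × 1.10 = 112.2, which rounds down to 112. The article does not state this, so it is an inference, but it gives the printed number. The same shortcut per group gives 34 × 1.10 = 37.4, which rounds up to 38. The shortcut therefore yields both printed figures if the total is rounded down and the group size up.

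**Step 4. Compare the two targets.**

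| | 112 | 114 |
|---|---|---|
| Per group (÷ 3) | 37.3 | 38 |
| Left after 10% loss | 112 × 0.90 = 100.8 | 114 × 0.90 = 102.6 |
| At least 102? | No | Yes |
| Largest loss that still leaves 102 | 1 − 102/112 = 8.9% | 1 − 102/114 = 10.5% |

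**Step 5. Effect on power, with the Step 1 formula.**

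| N | Power |
|---|---|
| 102.6 | 0.814 |
| 102 | 0.811 |
| 100.8 | 0.806 |
| 100 | 0.803 |
| 99 | 0.798 |

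A whole-number loss from 112 of 11 or 12 people leaves 101 or 100. Both are below 102, and both keep power above 0.80.

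**The case against.** The strongest reply is that nothing of consequence depends on this.

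- **Power is kept.** Because 102 was rounded up to give equal groups, there is some slack, and about 100.8 completers still give 0.806. This stands, and the point should not be read as a claim that the trial is underpowered.
- **The gap is small beside the uncertainty in the dropout rate.** The difference is 2 of 112, or 1.8%, while the 10% is a round figure taken from one earlier study. At 114 enrolled, an 11% loss would also leave fewer than 102 (114 × 0.89 = 101.5). This stands too, but it does not excuse a total that fails at the very rate the plan assumes.
- **Dropouts are not lost to the main analysis.** Statistical Methods specifies an intention-to-treat analysis of everyone randomised, using maximum likelihood for missing data. Participants who leave still contribute what was observed, so 100.8 counts completers, not the intention-to-treat set. This is fair. The shortfall bears most directly on the per-protocol analysis, although the section's own allowance is framed in terms of people lost.
- **Arms need not be exactly equal.** Under randomisation stratified by cancer type, final arm sizes can differ slightly, so 112 not being divisible by three is not a defect by itself. This is accepted, but the article states a planned size of 38 for each arm, and three such arms do not make 112.

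These replies limit the consequence. None of them reconciles 112 with 38 per group.

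**Conclusion.** The concern holds on both counts. The overall target (112) and the per-group target (38, hence 114) contradict each other under 1:1:1 allocation. At the assumed 10% loss, 112 leaves 100.8 against a stated requirement of 102. The per-group figure is the one consistent with the section's own inputs.

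The size is minor: two participants, and a power difference of about 0.005 (0.811 against 0.806), with both values above 0.80. The arithmetic on the two targets uses only figures printed in the article. The power figures also assume the between-groups repeated-measures F test, which the article does not name but which reproduces its 102. Whether that overall test suits the pairwise hypotheses is a separate question, not addressed here.

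**What to change.** In the Sample Size section, replace the total of 112 with 114 and keep 38 per group. Show the step: 102/(1 − 0.10) = 113.3, rounded up to 114 so that the three arms are equal. Check that any other place where the target is recorded, such as the full protocol, the randomisation list and the ethics committee report, carries the same 114.

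The cost is one corrected number. The article already plans 38 per arm, so no participants are added beyond what it states for each group.

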### Recruitment and Assignment to Interventions

Participants will be recruited at the Reina Sofia University Hospital in Córdoba (Spain). The oncology and nursing team will approach to possible participants following the inclusion and exclusion criteria of the protocol during their visits. Eligible participants will sign an informed consent before randomization. Participants will be randomly allocated to one of the three conditions of the study (face-to-face ACT + app/face-to-face ACT/waitlist group) in a ratio of 1:1:1 using computer-generated sets of numbers^1^ and stratified by cancer type (breast/lung/colorectal). Group assignment will be provided to the trial research team in closed opaque envelopes. Randomization and allocation concealment will be carried out by trial independent research staff.

### Blinding

Participants will receive information about the interventions but not about the main objectives of the study and which intervention is considered active. Also, members of the work group of the project involved in the assessment of the participants will be blinded to the objectives of the study and participants assignment.

### Instruments

Sociodemographics characteristics of the participants will be collected using a structured interview, including information about sex, age, marital status, education, professional activity, annual income, cancer type, treatment, and cancer stage. Also, the participants will be asked if they are currently taken psychiatric medication, and, if yes, the type of medication and daily dose. In addition, all the participants will complete the following questionnaires:

#### Acceptance and Action Questionnaire-II

This instrument is designed to assess experiential avoidance and psychological inflexibility through 7 items that are answered with a Likert-type scale from 1 (never true) to 7 (always true), with a higher score indicating greater experiential avoidance. The questionnaire has adequate psychometric properties in its original version (α = 0.84) and in its adaptation to Spanish (α = 0.75–0.93) (Ruiz et al., 2013). It has been widely used in cancer patients (González-Fernández and Fernández-Rodríguez, 2019).

#### Hospital Anxiety and Depression Scale

This scale is used to assess anxiety and depression in hospital settings. It is made up of 14 items (with two subscales; 7 for anxiety and 7 for depression), which are answered on a scale from 0 to 3, with maximum values of 21 in each of the subscales. The cut-off point for establishing the presence of anxiety and depression is set at 8 (probable case). This scale has been adapted and validated into Spanish, showing good psychometric properties (α = 0.86) (Zigmond and Snaith, 1983; Terol-Cantero et al., 2015).

